### Statistical analyses

Categorical parameters will be presented by means of frequencies (%). Continuous parameters will be summarized by mean ± standard deviation or median and interquartile range, where appropriate. All patients having a VCTE examination with valid measurements [8] will be included in the analysis population. Subjects excluded from the analysis will be compared to those having a VCTE examination with valid measurements using the Chi squared test and t-test for categorical or continuous characteristics respectively. Prevalence and its 95% confidence intervals (95%CI) of LSM ≥ 8 kPa will be computed overall (primary endpoint) and in the subgroup of patients with risk factors. Analogously, prevalence of CAP ≥ 250 dB/m and its 95%CI will be computed, overall and among patients with risk factors. Concordance between variables (LSM, fibrosis scores, CAP, steatosis scores, liver biopsy) will be computed. Scatter plots and Pearson’ r linear correlation coefficients will be used to explore the relationship between continuous variables, including LSM and fibrosis scores values. Receiver operating characteristic (ROC) curves, using LSM ≥ 8 kPa as the gold standard for fibrosis, will be computed for the different continuous fibrosis scores. Sensitivity, specificity, predictive values and likelihood ratios will be performed using LSM ≥ 8 kPa as the gold standard for fibrosis for different fibrosis categorized scores. Comparison of values obtained with M and XL probes in the assessment of LSM and CAP will be performed both, using the continuous forms of the variables with t tests (or non-parametric tests in the case these variables violate the necessary assumptions), and using the categorical variables using the 8 kPa and 250 dB/m^2^ cut-offs with Chi squared test. In addition, multivariate linear regression models and multivariate logistic regression models will be computed with LSM (or CAP) as the dependent variable (continuous for linear model and categorical for logistic mode) to assess the effect of the M or XL and potential interaction with the probe size. The relative frequency of adverse events to the study procedures will be reported in percent.

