#### Secondary outcome measures

Percentage of subjects with LSM by VCTE ≥ 8 kPa in the subgroup of patients with risk factors for chronic liver diseases at visit 1 and/or 2.Comparison of liver fibrosis diagnosis accuracy between VCTE and fibrosis scores (including NAFLD fibrosis score, FIB-4, Forns index and APRI score) in the general population and in the subgroup of patients with risk factors for chronic liver disease, at visit 1 and 2.Comparison of liver fibrosis diagnosis accuracy between VCTE, fibrosis scores and liver biopsy in the general population and in the subgroup of patients with risk factors for chronic liver diseases, in patients with a liver biopsy available at visit 2.Percentage of subjects with controlled attenuation parameter (CAP) ≥ 250 dB/m, either with M or XL probe, in the general population and in the subgroup of patients with risk factors for chronic liver diseases at visit 1 and/or 2.Comparison of liver steatosis diagnosis accuracy between CAP and steatosis scores (including fatty liver index (FLI), hepatic steatosis index (HSI), lipid accumulation product (LAP), index of NASH (ION) and NAFLD-liver fat score (NAFLD-LFS)) in the general population and in the subgroup of patients with risk factors for chronic liver diseases at visit 1 and 2.Comparison of liver steatosis diagnosis accuracy between CAP, steatosis scores (including FLI, HSI, LAP, ION and NAFLD-LFS) and liver biopsy in the general population and in the subgroup of patients with risk factors for chronic liver diseases, in patients with liver biopsy available at visit 2.Comparison of liver steatosis diagnosis accuracy between CAP and abdominal ultrasound in the general population and in the subgroup of patients with risk factors for chronic liver diseases, in patients with abdominal ultrasound available at visit 2.Comparison of values obtained with M and XL probes in the assessment of LSM and CAP using VCTE at visit 2.Cost-effectiveness and budgetary impact of a liver fibrosis screening program for liver fibrosis detection in the general population and in the subpopulation with risk factors for chronic liver diseases. Direct and indirect cost savings of early detection of liver fibrosis in subjects with risk factors for chronic liver diseases.Percentage of measurement failure during VCTE examination at visit 1 and 2.Percentage of patients with procedure-related adverse events (adverse events related to VCTE and/or liver biopsy) and serious adverse events during the duration of the study.Detection of common genetic variants, single nucleotide polymorphisms (SNPs), in patients with and without significant hepatic fibrosis or chronic liver diseases, including genome-wide association studies (GWAS) and whole-genome sequencing (WGS) in blood samples.Incidence of cirrhosis, liver cancer, and liver-related death and all-cause of mortality in patients with significant fibrosis and/or severe steatosis after 5 and 10 years from the first evaluation.Incidence of cardiovascular events in patients with significant fibrosis and/or severe steatosis after 5 and 10 years from the first evaluation.

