**BIOBANK**		
Blood samples: plasma, serum, DNA.	**X**	
**VC TRANSIENT ELASTOGRAPHY**	**X**	**X**
**ABDOMINAL ULTRASOUND**		**X**
**LIVER BIOPSY**		**X**
**AE assessment**	**X**	**X**

*AE* adverse event, *AP* alkaline phosphatase, *α1AT* α1-antitrypsin, *CRP* C-reactive protein, *HBV* hepatitis B virus, *HCV* hepatitis C virus, *TSH* thyroid stimulating hormone

**Liver fibrosis** will be estimated by three different methods: LSM, liver fibrosis scores and liver biopsy.LSM will be performed in all patients using VCTE. LSM will be performed with M or XL probe following the Automatic Probe Selection tool available on the Fibroscan®. LSM will be repeated at visit 2 in those patients referred to the university hospital. Significant liver fibrosis by VCTE will be defined by a LSM ≥ 8.0 kPa with either M or XL probe.Fibrosis scores/serum biomarkers: Four different established liver fibrosis scores using different blood tests will be determined at visit 1: NAFLD fibrosis score (NFS), Forns Index, Fibrosis-4 (FIB-4) and AST to Platelet Ratio Index (APRI). Significant liver fibrosis will be defined when the values of the different scores are above the following cut-offs, according to literature [8, 10]: NFS ≥ 0.676, Forns index ≥ 6.9, FIB-4 ≥ 2.67, APRI ≥ 1.50.Liver biopsy. In patients with a liver biopsy available, liver fibrosis will be assessed and defined according to SAF/NASH CRN Score [21] and analyzed by two central readers. Discrepancies between two readers will be re-assessed and discussed until consensus.

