#### Sample size calculation

The sample size for the LiverScreen project has been computed to answer the questions of 1/ the usefulness of TE as a screening method to detect significant liver fibrosis among the European general population ≥ 40 years, and 2/ the differences (if any) in the 5-year incidence of liver clinical outcomes (or cardiovascular events or mortality) between those with and without significant liver fibrosis (LSM ≥ 8 kPa). Because the gold standard for the staging of liver fibrosis remains liver biopsy, the sample size calculation of the study considers the final number of liver biopsies needed to evaluate the concordance between liver biopsy and VCTE. For an estimated prevalence of LSM ≥ 8 kPa of around 3%, assuming a 5% of bilateral alpha error and a statistical power of 95%, a sample size of 28,887 subjects would be required. If 3% of the study population have altered VCTE and only 50% of them agree to have a liver biopsy performed, we will have around 450-500 available liver biopsies. Considering all these factors, the sample size of the study will be of 30,000 subjects.

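### The fibrosis scores are judged against LSM ≥ 8 kPa as the gold standard for fibrosis, so the results show prediction of a positive VCTE, not accuracy for fibrosis

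*Protocol article*

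**What the plan says.** All references are to the protocol article.

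- **Secondary outcome measures**, second item: "Comparison of liver fibrosis diagnosis accuracy between VCTE and fibrosis scores (including NAFLD fibrosis score, FIB-4, Forns index and APRI score"), in the general population and the risk-factor subgroup, at visits 1 and 2. No independent reference is named.
- **Secondary outcome measures**, third item: "Comparison of liver fibrosis diagnosis accuracy between VCTE, fibrosis scores and liver biopsy in the general population" and in the risk-factor subgroup, restricted to those with a biopsy at visit 2.
- **Statistical analyses**: ROC curves, "using LSM ≥ 8 kPa as the gold standard for fibrosis, will be computed for the different continuous fibrosis scores", and "Sensitivity, specificity, predictive values and likelihood ratios will be performed using LSM ≥ 8 kPa as the gold standard for fibrosis" for the categorised scores. For the comparison with histology, the analysis named is concordance: "Concordance between variables (LSM, fibrosis scores, CAP, steatosis scores, liver biopsy) will be computed".
- **Sample size calculation**: "Because the gold standard for the staging of liver fibrosis remains liver biopsy", the calculation takes account of the number of biopsies needed to assess concordance with VCTE.
- **Measurements and investigation procedures**: "Four different established liver fibrosis scores using different blood tests will be determined at visit 1". Biopsies have two central readers. Table 1 schedules haematology at visit 1 only.
- **Study design**: biopsy is offered at visit 2 when LSM is above 8 kPa or when chronic liver disease is suspected.

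**The concern.** The article names two gold standards for the same condition. One of them, LSM ≥ 8 kPa, is the positive result of a method that the second secondary outcome sets against the scores. When one competitor defines the truth, the other's figures measure agreement with it. A score loses credit wherever it correctly disagrees with a wrong LSM and gains credit wherever it repeats LSM's error.

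The Discussion says the study will answer questions of diagnostic accuracy of non-invasive tests in a low-prevalence setting and will be a basis for diagnostic pathways. A table of score sensitivities headed as accuracy for fibrosis would be read in that light, and as evidence on whether blood scores can stand in for VCTE. The Study Rationale criticises earlier work for not confirming the diagnosis systematically by biopsy. The score analyses, as labelled, have the same weakness.

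**Working it through.** **1. Biopsies available (the article's own figure).** Inputs from Sample size calculation: 30,000 subjects, 3% with LSM ≥ 8 kPa, 50% biopsy uptake.

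30,000 × 0.03 × 0.50 = 450, the lower end of the stated 450 to 500.

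**2. What a score shows against LSM ≥ 8 kPa.** Let PPV be the proportion of LSM positives who truly have fibrosis, and Se and Sp the score's true sensitivity and specificity. If the errors of score and LSM are independent given true fibrosis status:

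apparent sensitivity = PPV × Se + (1 − PPV) × (1 − Sp)

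The article gives none of PPV, Se or Sp. All values below are assumptions, with Sp = 0.95 for the two imperfect scores.

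| PPV of LSM | Se 0.50 | Se 0.80 | Perfect score (Se = Sp = 1) |
|---|---|---|---|
| 100% | 0.500 | 0.800 | 1.00 |
| 80% | 0.410 | 0.650 | 0.80 |
| 70% | 0.365 | 0.575 | 0.70 |
| 60% | 0.320 | 0.500 | 0.60 |
| 50% | 0.275 | 0.425 | 0.50 |
| 40% | 0.230 | 0.350 | 0.40 |

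Worked entry: 0.5 × 0.50 + 0.5 × 0.05 = 0.275. Apparent specificity barely moves: for Se 0.80 it is 0.950 if every LSM negative is free of fibrosis and 0.946 if 99.5% are. The planned figures equal accuracy for fibrosis in general only if LSM ≥ 8 kPa makes no errors.

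**3. The direction is not fixed.** The term (1 − Sp) is the chance that the score is positive in an LSM false positive, if errors are independent. Call that chance f when they are not. At PPV 50% and Se 0.50 (kept at 0.50 among LSM true positives), apparent sensitivity = 0.25 + 0.5 × f:

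- f = 0.05 (independent errors): 0.275
- f = 0.50: 0.50, no distortion
- f = 1 (errors fully shared): 0.75, an overstatement

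**4. Would a plain head-to-head against biopsy cure it?** Not without correction. Biopsy is offered mainly when LSM is above 8 kPa, so biopsied participants are truncated on LSM but not on the scores. I simulated two equally accurate, independent, normally distributed markers with fibrosis prevalence 2% to 3%, selecting the top 3% on LSM, with no ALT route to biopsy and full uptake (all assumed).

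| ROC area, everyone (both markers) | LSM, selected only | Score, selected only |
|---|---|---|
| 0.85 | about 0.66 | about 0.85 |
| 0.92 | about 0.72 | about 0.92 |
| 0.96 | about 0.78 | about 0.96 |

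Two equally good tests look very unequal, this time to the disadvantage of LSM.

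**5. Visit 2.** The outcome asks for the VCTE-score comparison at visits 1 and 2, but the scores are determined at visit 1. APRI is by name the AST to platelet ratio. Table 1 repeats AST at visit 2 but not haematology, so no platelet count is scheduled for a visit-2 APRI.

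**The case against.** The strongest defence is that the analysis is sound and only its name is wrong. The article defines significant fibrosis by VCTE as LSM ≥ 8 kPa, and LSM is the only reference available in all analysed subjects. How well blood scores predict a positive VCTE is a fair question for a screening programme. Biopsy is not ignored either: there is a separate biopsy outcome, central double reading and a planned concordance analysis. A fuller analysis plan may specify accuracy against histology, so its absence from a condensed article is no fault.

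This stands as far as it goes, and it limits the point to the label and the inference. It does not remove the conflict, because the article states the reference standard outright and contradicts it in the section on sample size.

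A reader might infer more than the text supports:

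- **That VCTE is scored against itself and cannot lose.** No sensitivity, specificity or ROC curve for VCTE against its own cut-off is written; these measures are planned for the scores only.
- **That every false-positive LSM counts as a miss for a score.** It does so only when the score is negative.
- **That the result favours VCTE whatever the truth.** Step 3 of the working shows that shared errors can raise a score's apparent sensitivity.
- **That the bias enters the cost-effectiveness model.** The Health economic evaluation section takes transition probabilities from a validated progression model and later from follow-up. It names no score accuracy as an input.
- **That none of the scores can be compared at visit 2.** The documents show a missing component only for APRI, and the phrase could mean comparing each visit's LSM with the visit-1 scores.

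**Conclusion.** The concern holds as a wrong reference standard for a secondary outcome. The article contradicts itself on the gold standard for fibrosis. The LSM-referenced results measure prediction of a positive VCTE and cannot support conclusions on the accuracy of VCTE relative to the scores.

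That conclusion follows from the definitions and needs no outside figure. The size does need one. With independent errors and LSM PPV between 40% and 100%, a true sensitivity of 0.80 would appear as anything from 0.35 to 0.80; with shared errors the distortion could be smaller or reversed. The visit-2 wording is a minor inconsistency to be reconciled.

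The primary endpoint, the prevalence of LSM ≥ 8 kPa, is untouched. This should be fixed, but it does not threaten the study's main result.

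**What to change.** 1. In Secondary outcome measures and Statistical analyses, describe the LSM-referenced analyses as agreement with, or prediction of, LSM ≥ 8 kPa. Stop calling LSM the gold standard for fibrosis, and state that no conclusion on VCTE relative to the scores will be drawn from these analyses.
2. For accuracy for fibrosis, use the central-read biopsy stage as reference for both VCTE and the visit-1 scores in biopsied participants. Either limit claims to predictive value among those referred, or correct for partial verification with the method named in advance. Do not use an uncorrected paired comparison of ROC areas, because selection on LSM handicaps LSM.
3. Reconcile the visit 1 and 2 wording for the scores with the visit-1 determination and with Table 1.

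**Cost.** Items 1 and 3 are wording. Item 2 changes the analysis and needs no new data, since the biopsies and central reading are already planned. The drawback is that it rests on about 450 selected patients, so it is less precise, and a verification correction adds assumptions of its own.

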### Study design

This study is a single group screening study. It has been registered retrospectively on Clinicaltrials.gov (NCT03789825) the 14^th^ of November 2018. First patient included was in May 2018.

The present population-based study will include 30,000 subjects in eight European countries (Fig. 1). Eligible participants will be invited to attend at their primary care centre or at a research facility where a nurse will perform visit 1. This visit will include a detailed interview, physical examination, questionnaires related to alcohol consumption, quality of life and health status assessment, venipuncture for liver biochemical tests assessment and biobanking, and VCTE to assess LSM and controlled attenuation parameter (CAP). If participants show a LSM ≥ 8 kPa, unreliable or failed VCTE measurement [16] and/or increased ALT levels (ALT ≥ 1.5 x upper limit of normal value), they will be referred to second visit in a Liver Unit at the academic center for further evaluation (visit 2). Otherwise, the study finishes after completion of visit 1 (Fig. 2). Visit 2 will be completed by hepatologists within the 3 months following visit 1, according to a standardized work-up for liver disease diagnosis and evaluation. Visit 2 will include evaluation of the participant’s medical history, physical examination with complete liver tests, FibroScan examination and abdominal ultrasound. The FibroScan examination at visit 2 will be performed with both probes (M and XL). Afterwards, a liver biopsy will be offered to the patient for diagnosis and staging of liver disease when LSM is above 8 kPa or if chronic liver disease is suspected, as per standard of care.

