#### Primary outcome measure

Percentage of subjects with LSM by VCTE ≥ 8 kPa at any visit, either with the M or XL probe, in the general population.

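### The methods named for comparing the M and XL probes measure average differences or association, and none measures how closely the two readings agree within a patient

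*Protocol article*

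**What the plan says.** Both fibrosis rules in the protocol article accept either probe. The primary outcome is "Percentage of subjects with LSM by VCTE ≥ 8 kPa at any visit, either with the M or XL probe, in the general population". Under Measurements and investigation procedures, "Significant liver fibrosis by VCTE will be defined by a LSM ≥ 8.0 kPa with either M or XL probe". The same section applies one CAP cut-off of 250 dB/m to either probe. It also says how the probe is chosen: "LSM will be performed with M or XL probe following the Automatic Probe Selection tool available on the Fibroscan".

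Paired data come from visit 2. The Study design section states: "The FibroScan examination at visit 2 will be performed with both probes (M and XL"). A secondary outcome uses them: "Comparison of values obtained with M and XL probes in the assessment of LSM and CAP using VCTE at visit 2".

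The Statistical analyses section gives three methods for this comparison:

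- continuous values: "using the continuous forms of the variables with t tests (or non-parametric tests in the case these variables violate the necessary assumptions");
- classified values: "using the categorical variables using the 8 kPa and 250 dB/m^2^ cut-offs with Chi squared test" (the unit printed there differs from the dB/m used elsewhere, and I use dB/m);
- linear and logistic regression with LSM or CAP as the dependent variable, "to assess the effect of the M or XL and potential interaction with the probe size".

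The same section says that concordance will be computed among LSM, fibrosis scores, CAP, steatosis scores and biopsy. M against XL is not in that list. It has its own later sentence, with the methods above.

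**The concern.** Because one cut-off serves both probes, the useful question for the paired readings is whether a patient gets about the same value, and the same classification, from either probe. The named methods answer other questions. A t test asks whether the average difference is zero. A chi-squared test asks either whether two percentages differ or whether two classifications are associated, depending on the table used. The regression models estimate an average probe effect and its interaction. Within-patient differences in opposite directions cancel in all the averages.

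At stake is the usefulness of one secondary outcome. A non-significant result would not show that the probes agree. A significant one could reflect a small average shift. In both cases the paired readings, which the study collects anyway, would leave unreported the quantity most relevant to using a single cut-off.

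**Working it through.** The article gives no sample size, SD, margin or agreement limit for the probe comparison, so there is no figure of the plan to reproduce. The check shows what each named method responds to.

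**Inputs.** From the Sample size calculation section: 30,000 subjects and about 3% with LSM ≥ 8 kPa, so 30,000 × 0.03 = 900. This is used as an assumed number of pairs. It is not the visit 2 number, because participants with raised ALT or failed VCTE are also referred and some will not attend. Also assumed: log-normal true LSM with median 8 kPa and log-SD 0.35, independent errors for the two readings, and the mean and SD of the M−XL differences shown below.

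**1. The paired t statistic.** t = d̄ / (s/√n), where d̄ is the mean difference and s the SD of the differences; √900 = 30.

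- d̄ = 0 gives an expected t near 0 for any s, so poor agreement leaves no trace.
- d̄ = 0.2 kPa, s = 0.5 kPa: t = 0.2/(0.5/30) = 12.0.
- d̄ = 0.5 kPa, s = 2 kPa: t = 0.5/(2/30) = 7.5.

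The last two are both highly significant, but their limits of agreement, d̄ ± 1.96s, differ fourfold in width: ±0.98 against ±3.92 kPa around the mean.

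**2. Simulation, 1,000 runs of 900 pairs.** The last four columns are rejection rates at 5%.

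| d̄ (kPa) | s (kPa) | Limits around d̄ (kPa) | Classified differently at 8 kPa | Kappa | Paired t | Unpaired t | Chi-squared, two proportions | Chi-squared, cross-table |
|---|---|---|---|---|---|---|---|---|
| 0 | 0.5 | ±0.98 | 5.7% | 0.89 | 6.4% | 0.0% | 0.0% | 100% |
| 0 | 1 | ±1.96 | 11.1% | 0.78 | 5.1% | 0.0% | 0.0% | 100% |
| 0 | 2 | ±3.92 | 21.0% | 0.58 | 4.5% | 0.0% | 0.2% | 100% |
| 0 | 3 | ±5.88 | 28.4% | 0.43 | 4.8% | 0.1% | 0.5% | 100% |
| 0.2 | 0.5 | ±0.98 | 6.0% | 0.88 | 100% | 0.0% | 1.9% | 100% |
| 0.5 | 2 | ±3.92 | 21.0% | 0.58 | 100% | 99.8% | 87.6% | 100% |

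Down the first four rows agreement worsens steadily and no test column follows it.

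**3. The chi-squared test by hand.** Take rows 2 and 4 as tables with half the readings ≥ 8 kPa on each probe.

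- 11.1% of 900 ≈ 100 discordant: cells 400, 50, 50, 400.
- 28.4% of 900 ≈ 256 discordant: cells 322, 128, 128, 322.

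In both tables each probe puts 450 of 900 at or above 8 kPa. The difference in proportions is therefore 0, the probe odds ratio is (450/450)/(450/450) = 1, and McNemar's statistic is (50−50)²/100 = 0 or (128−128)²/256 = 0. On the cross-table, chi-squared = nφ²:

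- φ = (400² − 50²)/450² = 157,500/202,500 = 0.778, so 900 × 0.778² ≈ 544;
- φ = (322² − 128²)/450² = 87,300/202,500 = 0.431, so 900 × 0.431² ≈ 167.

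Both far exceed 3.84, and the larger value belongs to the better agreement. A significant cross-table result therefore shows association. Read as a probe difference, it would be read backwards.

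**4. What a discordance rate would deliver.** Its 95% CI half-width is 1.96√(p(1−p)/n). For p = 0.111 this is 1.96√(0.111 × 0.889/900) = 2.1 points, and for p = 0.284 it is 1.96√(0.284 × 0.716/900) = 2.9 points. If about 900 pairs are obtained, the two situations are clearly told apart.

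**The case against.** The strongest reply is that the stated outcome is a comparison of values, which the planned tests do carry out. The article does not call it a study of agreement, and nowhere says that a non-significant result will be taken as licence to pool the probes. That stands: the methods do not contradict the outcome's wording, and the point is an improvement to it.

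Four stronger readings are tempting, and the article does not support them.

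- *That the probes are compared only with tests of difference.* The regression models are also planned and give the size of an average probe effect, which partly answers the worry that a trivial shift may be significant. They still do not measure within-patient agreement.
- *That a large share of patients change class because of the probe.* The article gives no such data, and the simulation cannot show it. With zero mean difference and independent errors the two readings are exchangeable, so two readings from one probe would disagree as often. With other assumed inputs (median 9 kPa, log-SD 0.35, error of 10%, 15% or 20% per reading), discordance is about 12%, 17% and 22%, while the proportion ≥ 8 kPa is the same for both readings (62.7%, 62.2% and 61.5%). A 3% systematic difference hardly alters discordance (12%, 18%, 22%).
- *That an agreement analysis would settle whether the either-probe rule is sound.* At visit 1 the device tool selects the probe. At visit 2 one of the two probes may not be the one it would select. Visit 2 patients are also selected for high LSM, unreliable or failed VCTE, or raised ALT.
- *That the primary result is at risk.* It is a prevalence with a 95% CI, and the probe comparison does not enter it.

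A further reply is that agreement statistics are detail for an analysis plan that is not shown. That would hold if the article were silent. It names specific methods for this comparison, and its concordance sentence leaves the probe pair out.

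**Conclusion.** The concern holds as a limited point. The methods named for M against XL address mean shift, proportions or association, and none measures within-patient agreement. Paired readings are planned and one cut-off is applied to either probe. The conclusion follows from what the methods estimate and does not depend on the simulated values.

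The illustrated size, about 5% rejection by a paired t test with discordance anywhere from 5.7% to 28.4%, rests on an assumed LSM distribution, assumed measurement error and an assumed 900 pairs. It shows that the tests are insensitive to agreement. It gives no estimate of discordance in this study and no evidence of a probe effect. The consequence is confined to a secondary outcome, and the primary prevalence estimate is unaffected.

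**What to change.** In the Statistical analyses section, for the paired visit 2 readings, add:

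- the mean within-patient M−XL difference with 95% limits of agreement, for log LSM and for CAP;
- the M-by-XL cross-table at 8 kPa and at 250 dB/m, with the percentage classified differently, its 95% CI, and positive and negative agreement.

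Keep the difference tests and the regression models as supporting analyses, and say which table the chi-squared test uses, since on the cross-table it tests association.

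State the limits with the result: discordance includes ordinary repeat-measurement error; visit 2 patients are selected; and one of the two probes may not be the one the Automatic Probe Selection tool would choose. The analysis therefore informs the either-probe rule at visit 1 and does not by itself validate it.

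The cost is analysis wording only. Both probes are already planned at visit 2, so no measurement, participant or visit is added.

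### The M versus XL probe comparison at visit 2 is paired within patient, but the plan names a Chi squared test for the 8 kPa and CAP 250 cut-offs

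*Protocol article*

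**What the plan says.** All references are to the protocol article.

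- **Study design**, on the second visit: "The FibroScan examination at visit 2 will be performed with both probes (M and XL").
- **Secondary outcome measures**: "Comparison of values obtained with M and XL probes in the assessment of LSM and CAP using VCTE at visit 2".
- **Measurements and investigation procedures**, on LSM in all patients: "LSM will be performed with M or XL probe following the Automatic Probe Selection tool available on the Fibroscan". This gives one automatically chosen probe per examination, so visit 1 does not supply two readings per person. The two-probe data come from visit 2.
- **Statistical analyses**, continuous LSM and CAP by probe: "using the continuous forms of the variables with t tests", with a non-parametric fallback. Whether the tests are paired is not stated.
- **Statistical analyses**, dichotomised LSM and CAP by probe: "cut-offs with Chi squared test".
- **Statistical analyses**, linear and logistic models: "to assess the effect of the M or XL and potential interaction with the probe size". The data layout and error structure are not stated.
- **Statistical analyses**, excluded versus analysed subjects, which are two independent groups: "using the Chi squared test and t-test for categorical or continuous characteristics respectively".

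No paired method is named anywhere in the article.

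**The concern.** Each visit-2 patient contributes one M and one XL result at each cut-off. The question is whether the two probes classify the same patients differently, and only patients with discordant results carry information on that. A Chi squared test does not use that structure, whichever of two ways it is run:

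1. **On the two proportions** (share positive by M against share positive by XL), it uses the variance for two separate samples. Two readings of the same liver are expected to be positively correlated, so that variance is too large.
2. **On the 2×2 table of M result by XL result**, it tests whether the two results are associated. They will be, even if the probes classify equally often, so the p-value says nothing about a difference.

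At stake is the conclusion on probe interchangeability at the 8 kPa and CAP 250 cut-offs. The two-proportion version could miss a real difference. The cross-table version could be misread as showing one.

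**Working it through.** The article gives no sample size, power or error rate for this comparison, so there is no stated figure to reproduce.

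**Inputs**
- Number of pairs: about 900, from 3% × 30,000 (Sample size calculation). Referrals for raised ALT or failed VCTE would add to this, and non-attendance at visit 2 would reduce it.
- Two-sided alpha: 5%.
- Share positive: about 50% on each probe (assumption).
- Correlation between probes: not in the article. Assumed bivariate normal with latent correlation ρ from 0.5 to 0.9. At 50% positive, the correlation of the two binary results is φ = (2/π)·arcsin ρ.

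**Step 1. True type I error of the two-proportion Chi squared test**

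The true variance of the difference is (1 − φ) times the variance the test assumes, so true alpha = 2·[1 − Φ(1.96/√(1 − φ))].

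| ρ | φ | true alpha |
|---|---|---|
| 0.5 | 0.333 | 1.6% |
| 0.7 | 0.494 | 0.6% |
| 0.8 | 0.590 | 0.2% |
| 0.9 | 0.713 | 0.03% |

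For any φ > 0 the result is below 5%. In simulation (4,000 runs, 450 and 900 pairs, ρ 0.5 to 0.9), McNemar's test rejected 4.7% to 5.7% of the time under no difference.

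**Step 2. Power for a 5-point difference (52.5% against 47.5%), 900 pairs, ρ = 0.8**

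- Discordant shares under the model: 12.93% and 7.93%, total 20.86%.
- True SE of the difference: √[(0.2086 − 0.05²)/900] = 0.01513.
- Chi squared rejects when the difference exceeds 1.96 × √(2 × 0.25/900) = 1.96 × 0.02357 = 0.0462. Power = Φ[(0.05 − 0.0462)/0.01513] = Φ(0.25) ≈ 60%.
- McNemar rejects when it exceeds 1.96 × √(0.2086/900) = 1.96 × 0.01522 = 0.0298. Power = Φ[(0.05 − 0.0298)/0.01513] = Φ(1.33) ≈ 91%.

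The same formulas at other correlations, 900 pairs:

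| ρ | Chi squared | McNemar |
|---|---|---|
| 0.5 | 58% | 74% |
| 0.7 | 59% | 84% |
| 0.8 | 60% | 91% |
| 0.9 | 62% | 97% |

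**Step 3. An illustrative table**

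Take 900 pairs: 400 positive on both, 90 positive on M only, 50 positive on XL only, 360 negative on both. The shares positive are 490/900 and 450/900, a difference of 40/900 = 4.4 points.

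- Chi squared on the two proportions: (0.0444/0.02355)² = 3.56, p = 0.059.
- McNemar: (90 − 50)²/(90 + 50) = 11.43, p = 0.0007.

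**Step 4. The cross-table version**

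Take 400 positive on both, 400 negative on both, and 50 discordant each way. Both probes are positive in 450/900, so there is no difference, and McNemar's statistic is 0. Pearson's Chi squared on the cross-table is 900 × (400 × 400 − 50 × 50)²/450⁴ = 544. In simulation with no probe difference it rejected in 100% of runs at ρ of 0.5 or more.

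**The case against.** **McNemar's statistic is itself referred to a chi-squared distribution, so the wording might be shorthand.** This does not hold up well. The same section uses the same test name for excluded versus analysed subjects, who are independent groups, and never mentions pairing. Nor is this detail left to a fuller document: the article names a test, and the named test does not fit the design.

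A reader might infer more than the article supports, in four ways:

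- **That the t tests are wrong.** They are unspecified, not unpaired. A paired t test or a signed-rank test fits the wording, and a condensed article can leave that word out. Clarification is enough.
- **That the regression models are wrong.** The article does not say that both readings per patient enter one model. The phrase about interaction with probe size is loose and may mean covariate-by-probe interaction. A patient-level term is needed only if both readings are used.
- **That false positives are inflated.** On the two-proportion reading the reverse is true: the test is conservative and the cost is power. Only the cross-table reading rejects regardless of any difference.
- **That referral or the primary outcome is compromised.** Referral from visit 1 follows that visit's VCTE and ALT results. The primary prevalence, which counts a value of at least 8 kPa on either probe, is estimated separately. Neither uses the M versus XL test.

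It is also fair to say that the continuous comparison, if paired, would be sensitive: simulated power was 85% to 100% for an assumed 0.1 SD shift with 900 pairs. That limits the harm, but a shift in the mean does not show how often the probes classify patients differently at a cut-off.

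**Conclusion.** The point holds for the Chi squared test: the data are paired by design, and the named test suits independent groups. That it is conservative on the two-proportion reading needs only a positive within-patient correlation. The size of the loss depends on assumptions the article does not supply: the correlation, about 50% positive, about 900 pairs and a 5-point difference. Over latent correlations of 0.5 to 0.9, Chi squared power stays at 58% to 62% while McNemar's rises from 74% to 97%.

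The two estimated proportions themselves are unaffected; what suffers is the test and any interval built on independent samples. The t tests and regressions need clarification, not correction. Because the effect is confined to one secondary outcome, this is a should-fix point, not a must-fix one.

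**What to change.** In Statistical analyses:

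1. For the 8 kPa and CAP 250 cut-offs, replace the Chi squared test of M against XL with McNemar's test, and report the paired difference in proportions with its 95% CI.
2. State that the continuous comparison is paired: paired t test, or Wilcoxon signed-rank test as the non-parametric alternative.
3. State whether both readings per patient enter the linear and logistic models. If so, include a patient-level term through a mixed model or GEE.

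Bland-Altman limits of agreement, analysis of LSM on the log scale and a probe-by-BMI interaction would be useful but are optional.

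The cost is a change of wording. Both readings are already planned at visit 2, so no new data are needed.
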